### Study design and setting

This is a multi-centre, blinded, randomized study (Fig. 2). The study will take place at five emergency medicine (EM) residency programs across North America (4 Canadian- and 1 US-based centres). All EM residents PGY1–5 are eligible and will be invited to participate. Written consent will be obtained from all study participants. There are no exclusion criteria. We received research ethics board approval from all participating institutions.

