#### Self-guided learning

In the self-guided learning group, participants will observe the procedure demonstrated by an instructor, followed by self-guided practice using the same equipment and working environment as the DP + ML group. During practice, feedback will only be provided following an explicit participant request. Participants will be informed that they can complete their training at their own discretion, once they report feeling comfortable with the procedure.

Finally, participants from both groups will perform a video-recorded attempt immediately following completion of their respective practice sessions and complete a post-training survey.

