### Skill retention

Skill retention will be evaluated at 6 to 12 months following the initial training session. Due to logistical challenges related to resident schedules (e.g. away on elective, off-service), we require a 6 month time frame to maximize participation. Each participant will perform a video-recorded BAC on the same task trainer used during their training sessions followed by a post-training retention survey.

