### Primary outcome

The primary outcome is the difference in skill performance of BAC between the two groups at post-training, assessed using a previously validated 7-point global rating scale (GRS) [22, 39]. Video recordings will be scored by three independent airway experts (2 Royal College certified emergency physicians, 1 staff anesthesiologist) trained in BAC. All reviewers will receive training from study investigators followed by practice video review to ensure scoring standardization. All reviewers will be blinded to the subjects’ identities and group allocation.

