### Statistical analysis

The survey data will be analyzed using descriptive statistics. The primary outcome (GRS) score will be evaluated using a repeated measures ANOVA with between subject factor of instruction (DP + ML or SG group) with one within subject factor of assessment repeated 3 times (pre, post, and retention). SPSS software (SPSS Inc. 18.0, Chicago IL) will be used for data analysis. 2-sided *P* < 0.05 is considered statistically significant for the primary outcome. Interrater reliability (IRR) for the reviewers’ scores will be analyzed using an intraclass correlation, after reviewing the same 20 videos. If a target IRR of ≥0.7 is achieved, the rest of the videos will be scored by one reviewer. Confidence ratings will be compared with GRS at pre-training, post-training and retention using Spearman’s correlations.

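### The primary post-training comparison is tied to a three-time-point repeated measures ANOVA, which drops residents who miss the later, secondary retention session

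*Protocol article*

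**What the plan says.** Under Primary outcome, the protocol article fixes both the endpoint and its time: "The primary outcome is the difference in skill performance of BAC between the two groups at post-training". Under Self-guided learning it says when that measurement is taken: "participants from both groups will perform a video-recorded attempt immediately following completion of their respective practice sessions".

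The retention measurement is separate and later: "Skill retention will be evaluated at 6 to 12 months following the initial training session" (Skill retention). The GRS score at that visit is listed under Secondary outcomes. The article expects difficulty in getting residents back and widens the window for that reason: "Due to logistical challenges related to resident schedules (e.g. away on elective, off-service), we require a 6 month time frame to maximize participation".

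Under Statistical analysis, one model is named for the primary outcome: "The primary outcome (GRS) score will be evaluated using a repeated measures ANOVA with between subject factor of instruction", with "one within subject factor of assessment repeated 3 times (pre, post, and retention"). The software is also named: "SPSS software (SPSS Inc. 18.0, Chicago IL) will be used for data analysis". No separate analysis of the post-training score is described.

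Sample size determination gives 80 residents per group and 80% power for a difference of 1.3 GRS points at α = 0.05. It rests on a between-groups comparison. It states no SD and no allowance for loss.

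**The concern.** The endpoint and the model do not fit each other. The endpoint is complete on the training day. The model needs a third score taken 6 to 12 months later. Classical repeated measures ANOVA, including the repeated measures procedure of the general linear model in the named software, removes any subject with a missing level of the within-subject factor.

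Followed as written, the plan would discard primary-outcome data already in hand because of absence from a secondary visit. Two things are at stake. The first is precision, because the trial was sized on 80 per group with no margin. The second is the population: the primary result would describe residents who came back, not all those randomised and assessed after training.

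**Working it through.** **Step 1. Set the statements side by side.**

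| Item | Protocol article | Section |
|---|---|---|
| Primary endpoint | GRS difference at post-training | Primary outcome |
| When measured | Immediately after practice | Self-guided learning |
| Retention GRS | Secondary, 6 to 12 months | Secondary outcomes; Skill retention |
| Model for the primary outcome | Repeated measures ANOVA over pre, post and retention | Statistical analysis |
| Allowance for loss | None stated | Sample size determination |

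A resident with pre and post scores but no retention score has the primary outcome observed, yet cannot enter the named model.

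**Step 2. The plan's own figure.** The stated power cannot be reproduced independently because no SD is given. It can be solved backwards. With n = 80 per group, a difference of 1.3, two-sided α = 0.05 and 80% power, the normal approximation gives

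SD = 1.3 / [(1.960 + 0.842) × √(2/80)] = 1.3 / (2.802 × 0.1581) = 2.93.

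The t-test version gives a standardised difference of 0.4457, so SD = 1.3 / 0.4457 = 2.92. Both are about 2.9.

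**Step 3. Residents left under an assumed loss.** The loss rate is an assumption.
- 20% loss: 80 × 0.8 = 64 per group, so 160 − 128 = 32 existing post-training scores are discarded.
- 30% loss: 80 × 0.7 = 56 per group, so 160 − 112 = 48 are discarded.

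**Step 4. Power for 1.3 points at post-training.** This is a two-sided two-sample t-test with noncentrality (1.3/SD) × √(n/2). At SD 2.92 that is 0.4457 × √32 = 2.52 for n = 64, and 0.4457 × √28 = 2.36 for n = 56.

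| SD (assumed) | 80 per group | 64 per group | 56 per group |
|---|---|---|---|
| 2.92 (implied by the plan) | 80% | 71% | 65% |
| 2.5 | 91% | 83% | 78% |
| 2.0 | 98% | 95% | 93% |
| 1.5 | above 99% | above 99% | above 99% |

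The normal approximation agrees to within about one percentage point. At the implied SD, the difference detectable with 80% power rises from 1.3 to 1.45 points at 20% loss and to 1.55 at 30%. If every post-training score is used, the first column applies whatever the attendance at retention.

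**Step 5. Bias.** An illustrative simulation set the true post-training difference at 0.5 SD, with about 15% to 21% missing retention. The difference among completers was:
- 0.49 SD when loss was completely random (0.49 in all simulated residents);
- 0.46 SD when attendance depended on the post-training score in the same direction in both arms;
- 0.76 SD when the direction was opposite in the two arms.

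Only the last is a material distortion.

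**The case against.** **The exclusion is inferred.** The article names a model; it does not say that residents with incomplete scores are left out. Missing-data rules are commonly left to an analysis plan, and none is shown. That is fair as far as it goes. But the model is stated, it is the only one given for the primary outcome, and dropping incomplete subjects is a property of it. An analysis plan could avoid the loss only by adding to or departing from what the article says.

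**The power loss may be small.** This stands. An SD near 2.9 is very large for a score running from 1 to 7, where the maximum possible is about 3.0; the article does not say whether the score is a single 7-point rating or a sum of items. With an SD of 2.0 or less, little power is lost.

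**Stronger readings that the article does not support.**
- A reader might infer that the randomised comparison is broken. The reasons given for absence are electives and off-service work, and nothing suggests that these differ by arm. Selection by training year, fixed before randomisation, would narrow the population without in itself biasing the comparison.
- Because "All EM residents PGY1–5 are eligible and will be invited to participate", a reader might infer that final-year residents will have left by the retention session. The article gives neither the time of year of training nor the spread across years, so this is possible but not established.
- A reader might attribute low power of the group-by-time interaction to dropout. Such figures need a correlation and a degree of retained effect that the article does not supply. In an illustration with correlation 0.3 and half the effect retained, power was already 56% with full attendance, so most of that shortfall comes from the choice of test.

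**The wide window is a mitigation.** Also fair: it exists to raise attendance. It does not make attendance complete, and it shows that the difficulty was foreseen.

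**Conclusion.** The point holds as a mismatch between a stated endpoint and a stated method. The primary outcome is complete on the training day, but the named analysis conditions it on attendance 6 to 12 months later.

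The consequence is conditional. With full attendance there is none. Otherwise the loss of power depends on attrition and SD, both assumed here. On the plan's own implied SD it is appreciable (about 9 points at 20% loss and 15 at 30%). At an SD of 2.0 it is about 3 and 5 points, and at 1.5 it is negligible. Serious bias would require attendance to relate to performance differently in the two arms, and the article gives no ground to expect that.

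The case for change does not rest on the worst row of the table. Restricting the primary comparison to returners serves no purpose and is avoidable at any SD.

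**What to change.** State that the primary analysis is the between-group contrast in GRS at post-training, in every randomised resident with a post-training video, whether or not the resident returns for retention. Either of two forms will do, and one should be named in advance:

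1. a comparison of post-training scores adjusted for the pre-training score (ANCOVA); or
2. the post-training contrast from a likelihood-based linear mixed model on all available pre, post and retention scores.

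For the secondary retention comparison, use that mixed model in place of the repeated measures ANOVA, so that residents with partial data still contribute.

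The cost is a change of analysis wording before the data are analysed. No further residents, visits or measurements are needed, and the named software has a mixed-model procedure. By contrast, keeping 80 complete cases per group under the present model would need about 80 / 0.8 = 100 per group at 20% loss, or 80 / 0.7 ≈ 115 at 30%.

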## Discussion

The unique challenges of postgraduate training in medicine demands that research seeks to enhance our understanding of optimal simulation-based instructional methods rather than further highlighting the benefits of hands-on practice when compared to non-simulation-based teaching [42]. While the benefits of ML + DP in simulation are promising, we should acknowledge that it is a complex intervention with a variety of elements that differ as a result of local circumstances and resource availability [2]. The resources required to implement DP + ML cannot be understated. There is often more equipment, trainers, and time required with this method [15]. In a similar study comparing simulation-based deliberate practice with self-guided practice on ultrasound regional anesthesia skills, subjects in the self-guided practice group spent an average of 6.8 min practicing compared to 48.2 min in the deliberate practice group.

Currently, there is a paucity of data to inform preferred methods of simulation-based procedural training. McGaghie et al. concluded in their 2011 meta-analysis that “only a small number of studies were identified that address head-to-head comparative effectiveness of SBME with deliberate practice and traditional clinical education or a preintervention baseline” [2]. A more recent systematic review and meta-analysis concluded that “limited evidence suggests” the superiority of mastery learning SBME over other techniques [15]. The authors noted that few studies compare ML with other simulation-based instructional methods, such as self-guided practice, with mixed results. In one study, anesthesia residents learning ultrasound guided regional anesthesia were randomized to either DP + ML or self-guided practice. The authors reported that while performance improved among both groups, there were no differences in participant skill performance or retention between groups [8]. In contrast, a study of medical students learning ultrasound guided regional anesthesia techniques concluded that the deliberate practice resulted in fewer errors compared to self-guided practice [19]. Both of these studies are subject to important limitations including a small sample size at a single institution. There remains uncertainty as to whether these findings can be extrapolated among a larger study population across multiple sites. Recently, a large, comparative, single site study of undergraduate medical trainees concluded mastery learning with simulation is superior to simulation without mastery learning for peripheral venous catheter insertion [43]. This certainly supports the use of ML in the undergraduate setting, however, its utility in postgraduate training requires further study.

Our study addresses this by comparing two different simulation-based instructional methods for EM residents using a large sample size at multiple centres. This study design seeks to overcome the limitation of generalizability—common among other single site SBME-based studies. In addition, the rarity and relative novelty of the BAC procedure itself minimizes baseline variation in prior experience skill.

This study has several limitations. Given that both teaching and testing occur with a low-fidelity simulator, our study is designed only to assess procedural skills rather than the decision making and non-technical skills of an interprofessional resuscitation. Due to logistical constraints, retention data collection will take place between 6 to 12 months rather than at a single point in time. Although all study participants will voluntarily enrol, we cannot guarantee their motivation to learn and improve, which is a key aspect of deliberate practice.

In conclusion, this study will have important implications for residency training as it will provide insight for medical educators involved in the design of simulation-based technical skills training. High quality simulation-based skills training is a promising method to improve clinical outcomes and patient safety [44]. At a system-based level, this study will aid administrators and medical education leaders in their decision making for resource allocation towards skills training and inform future curricular designs.

## Abbreviations

BAC: Bougie-assisted cricothyroidotomy
DP: Deliberate practice
GRS: Global rating scale
IRR: Interrater reliability
ML + DL: Mastery learning and deliberate practice
ML: Mastery learning
SBME: Simulation-based medical education
